# Safety and Optimal Neuroprotection of neu2000 in acute Ischemic stroke with reCanalization: study protocol for a randomized, double-blinded, placebo-controlled, phase-II trial

**DOI:** 10.1186/s13063-018-2746-9

**Published:** 2018-07-13

**Keywords:** Endovascular recanalization, Ischemia and reperfusion, Neuroprotectants, Collateral

## Abstract

**Background:**

The potential of neuroprotective agents should be revisited in the era of endovascular thrombectomy (EVT) for acute large-artery occlusion because their preclinical effects have been optimized for ischemia and reperfusion injury. Neu2000, a derivative of sulfasalazine, is a multi-target neuroprotectant. It selectively blocks *N*-methyl-D-aspartate receptors and scavenges for free radicals. This trial aimed to determine whether neuroprotectant administration before EVT is safe and leads to a more favorable outcome.

**Methods:**

This trial is a phase-II, multicenter, three-arm, randomized, double-blinded, placebo-controlled, blinded-endpoint drug trial that enrolled participants aged ≥ 19 years undergoing an EVT attempt less than 8 h from symptom onset, with baseline National Institutes of Health Stroke Scale (NIHSS) score ≥ 8, Alberta Stroke Program Early CT score ≥ 6, evidence of large-artery occlusion, and at least moderate collaterals on computed tomography angiography. EVT-attempted patients are randomized into control, low-dose (2.75 g), and high-dose (5.25 g) Neu2000KWL over 5 days. Seventy participants per group are enrolled for 90% power, assuming that the treatment group has a 28.4% higher proportion of participants with functional independence than the placebo group. The primary outcome, based on intention-to-treat criteria is the improvement of modified Rankin Scale (mRS) scores at 3 months using a dichotomized model. Safety outcomes include symptomatic intracranial hemorrhage within 5 days. Secondary outcomes are distributional change of mRS, mean differences in NIHSS score, proportion of NIHSS score 0–2, and Barthel Index > 90 at 1 and 4 weeks, and 3 months.

**Discussion:**

The trial results may provide information on new therapeutic options as multi-target neuroprotection might mitigate reperfusion injury in patients with acute ischemic stroke before EVT.

**Trial registration:**

ClinicalTrials.gov, ID: NCT02831088. Registered on 13 July 2016.

**Electronic supplementary material:**

The online version of this article (10.1186/s13063-018-2746-9) contains supplementary material, which is available to authorized users.

## Background

Recent clinical trials of endovascular thrombectomy (EVT) have shown a remarkably positive effect on the functional outcome of patients with acute ischemic stroke presenting with proximal anterior circulation occlusion [1]. However, a considerable number of individuals with stroke still remain disabled despite a higher rate of reperfusion and a striking improvement in clinical outcome by the recent use of stent retrievers [2]. Numerous endeavors have been devoted to attenuating neuronal cell death after ischemic injury, and “excitotoxicity” is considered one of the therapeutic targets for neuroprotection in acute ischemic stroke [3]. Herein, *N*-methyl-D-aspartate (NMDA) receptors play a role in excitatory neurotransmission, and their overactivation results in neuronal death after acute ischemic stroke. NMDA-receptor antagonists prevent such excitatory action of glutamate and cellular calcium overload. Unfortunately, no randomized controlled trials have succeeded in demonstrating the clinical efficacy of such drugs [4]. Potential reasons for the failure are explained by modeling mismatch between preclinical experiments and human stroke, adverse effects of the drugs, inappropriate time window, or complexity of the ischemic cascade [5]. Such limitations are being resolved with improvements in therapeutic strategies. First, the potential of neuroprotective agents as a promising treatment strategy in patients with acute ischemic stroke is being revisited in the EVT era because their preclinical efficacy has been optimized in ischemia and reperfusion models [6]. In this regard, neuroprotective actions of drugs may be optimized when cerebral blood flow is restored in actual clinical practice for acute ischemic stroke. Second, to address the complexity of the ischemic cascade, a multi-target neuroprotective modality, such as therapeutic hypothermia, is gaining evidence in cardiac arrest [7]. Such multi-step or multi-target treatment would be highly beneficial after recanalization in patients with acute ischemic stroke [8].

Neu2000 (a derivative of sulfasalazine) is a novel, multi-target neuroprotectant that combines modest (micromolar) NR2B subtype-selective blockade of NMDA receptors with potent (nanomolar) scavenging of reactive oxygen species [9, 10] (Fig. 1). It has been suggested that the prior failure of more potent, and subtype-unselective NMDA-receptor antagonist drugs in stroke trials may have been partly due to excessive reduction of intracellular free calcium levels and consequent enhancement of ischemic neuronal apoptosis [11]. Neu2000 seeks to blunt acute excitotoxicity without risking this downside, and then to additionally target downstream free-radical damage, which is prominently triggered by vascular reperfusion. The neuroprotective potential of Neu2000 has been well demonstrated in preclinical animal stroke models with a favorable efficacy and a wide range of therapeutic window profile [9, 10, 12, 13]. In human phase-I studies, there are no serious adverse events including psychosis [14]. The current trial aims to provide proof-of-concept for use of Neu2000 as an adjunct neuroprotective agent together with state-of-the-art EVT in patients presenting to stroke centers with acute ischemic stroke.

**Fig. 1 Fig1:**
[figure not shown]
Simplified illustration of possible mechanisms after Neu2000 administration to mitigate reperfusion injury in the setting of recanalization treatment. **a** Ischemic cascade after stroke and proposed effect of multi-target neuroprotection. **b** The expected effect of reperfusion with multi-target neuroprotection on burden of cell damage and functional outcome

## Methods

### Design

The Safety and Optimal Neuroprotection of neu2000 in acute Ischemic stroke with reCanalization (SONIC) trial is a multicenter, national, prospective, randomized, three-arm, parallel-group, double-blinded, placebo-controlled, phase-II clinical study with blinded-endpoint evaluation carried out in the Republic of Korea. This study aims to examine the effects of neuroprotectants in EVT-attempted patients within 8 h of stroke onset. All participating centers had received Institutional Review Board approval prior to trial initiation. Emergency medical consent is obtained from caregivers before study enrollment. Approval was obtained from the Institutional Review Board of each center. The flowchart of this study is shown in Fig. 2. The Standard Protocol Items Recommendations for Interventional Trials (SPIRIT) checklist is attached as Additional file 1.

**Fig. 2 Fig2:**
[figure not shown]
The flowchart of SONIC trial. *CT* computed tomography, *CTA* computed tomography angiography, *IV* intravenous, *tPA* tissue plasminogen activator, *ASPECTS* Alberta Stroke Program Early CT Score, *IP* investigational product, *MRI* magnetic resonance imaging

### Patient population

We will enroll acute ischemic stroke patients with moderate to severe neurological deficits (at least National Institutes of Health Stroke Scale (NIHSS) score ≥ 8) and imaging confirmation of proximal vessel occlusion in the anterior circulation. Before randomization, local investigators will assess imaging criteria with the Alberta Stroke Program Early CT Score (ASPECTS), definite proximal artery occlusion, and collateral status on baseline computed tomography (CT) and CT angiography (Fig. 2). Detailed study inclusion and exclusion criteria are shown in Table 1.

**Table 1 Tab1:** Study inclusion and exclusion criteria

Inclusion criteria	
1. Age ≥ 19 years	
2. Subject who is presented to hospitals after onset of brain ischemic symptoms from the base of last normal state and can start endovascular therapy in accordance with standard practice guidelines within 8 h after the symptom onset	
3. NIHSS ≥8 at screening time point	
4. Subject whose activity is possible without the help of others in the general condition 1 day before the ischemic stroke onset and prestroke Barthel Index scores > 90	
5. Subject whose cerebral CT and CTA imaging confirm acute ischemic stroke and symptomatic intracranial occlusion at screening and whose occlusion site considered the cause of acute ischemic stroke meets the following conditions: T- or L-type ICA occlusion, MCA M1 occlusion, MCA-M1 equivalent (2 or more MCA-M2, anterior temporal artery is not regarded M2)	
6. Subject with ASPECTS ≥ 6 on cerebral non-contrast CT	
7. Subject who spontaneously submit a written informed consent to participate in this trial	
Clinical exclusion criteria	
1. A medical history of hypersensitivity against aspirin (salicylates), sulfasalazine, or 5-ASA	
2. Subject whose heart diseases were confirmed at screening: Subject who was diagnosed with myocardial infarction within 6 months; subject who had severe arrhythmia evoking clinical symptoms (respiratory difficulties, tachycardia, etc.) within 6 months; subject whose ECG measured at the emergency room confirms the following results: A. pulse rate < 50 or > 120 beats/min. B. 2nd or 3rd degree AV block. C. congenital or acquired QT syndrome. D. ventricular pre-excitation syndrome	
3. Subject who was diagnosed with heart failure ≥ New York Heart Association class II Class I: patients with no limitation of activities; they suffer no symptoms from ordinary activities Class II: patients with slight, mild limitation of activity; they are comfortable with rest or with mild exertion Class III: patients with marked limitation of activity; they are comfortable only at rest Class IV: patients who should be at complete rest, confined to bed or chair; any physical activity brings on discomfort and symptoms occur at rest	
4. Subject who has a contraindication to iodinated contrast media	
5. Subject who is receiving renal replacement therapy such as dialysis due to acute or chronic renal failure	
6. Subject who is diagnosed with cancer or received cancer therapy within 6 months or has recurrent or metastatic cancer	
7. Subject who shows a high body temperature of 38 °C or more or who need antibiotic therapy due to infectious diseases	
8. Subject who takes pharmacotherapy for liver diseases such as hepatitis or liver cirrhosis	
9. Subject who is pregnant or lactating. In case of women of child-bearing potential, only subjects who are confirmed as not being pregnant can participate in this trial	
10. Subject who participated in other clinical studies within the past 3 months. In case of participation in an observational study without medication, the subject can participate in this trial	
11. Subject who was determined inappropriate for participation in this trial due to other reasons	
Imaging exclusion criteria	
1. Baseline CT evidence of intracranial hemorrhage 2. Baseline CT evidence of intracranial tumor on presentation 3. Baseline CTA shows that the site of occlusion considered to be the cause of acute ischemic stroke meets the following conditions: A. MCA + PCA or MCA + ACA occlusion in carotid T/L-type B. Occlusion of a bilateral intracranial large artery C. Simultaneous involvement of anterior and posterior circulation 4. Absence of the collateral circulation corresponding to one of the followings: CTA imaging shows absence or minimal collateral circulation at ≤ 50% of MCA territories, compared with pial filling of the contralateral side	

*NIHSS* National Institutes of Health Stroke Scale, *CT* computed tomography, *CTA* computed tomography angiography, *ICA* internal carotid artery, *MCA* middle cerebral artery, *ASPECTS* Alberta Stroke Program Early CT Score, *ASA* aminosalicylate, *ECG* electrocardiography, *PCA* posterior cerebral artery, *ACA* anterior cerebral artery

### Randomization

Participants will be randomly assigned in a 1:1:1 fashion to one of three arms: (1) high-dose, (2) low-dose, or (3) placebo. Randomization is based on computer-generated cards before study initiation and will be handed to authorized personnel in a sealed envelope. All study investigators and participants are masked to treatment allocation except investigational product (IP)-preparing personnel. The randomization schedule is not accessible except for safety reasons, until completion of this trial. Study drugs and the placebo are provided in an identical package.

### Treatment

A study subject is enrolled after clinical judgment with inclusion and exclusion criteria on the basis of acute-onset neurological manifestation, confirmed by imaging for arterial vessel occlusion. Written informed consent is obtained from the patient or a legal representative before enrollment. After enrollment, the study subject undergoes rapid endovascular recanalization therapy. The neuro-interventionist uses any available modality (stent retriever or aspiration thrombectomy) or its combination to achieve safe recanalization. In addition, the use of a balloon-guided catheter is recommended in the relevant internal carotid artery. All groups will receive the best current standard of care as described in the current local guidelines for acute stroke management: This represents the fact that they will receive tissue plasminogen activator intravenously in a 4.5-h window if they meet the accepted criteria [15].

The assigned groups are injected with intravenous administration of IP as a high-dose, low-dose, or placebo of Neu2000KWL (2-hydroxy-5-(2,3,5,6-tetrafluoro-4-trifluoromethyl-benzylamino)-benzoic acid) before recanalization attempt by the personnel who are blinded to treatment allocation. The first infusion is intended to be initiated before thrombus retrieval. Subsequent injection will be administered twice per day (12-h interval) during five consecutive days. In the high-dose group, the initial infusion dose is 750 mg mixed with 250 mL of saline; the subsequent nine doses are 500 mg (total dose: 5250 mg). In the low-dose group, the initial infusion dose is 500 mg, and the subsequent nine doses are 250 mg (total dose: 2750 mg). The placebo group receives 250 mL of saline 10 times. The infusion volume is 250 mL in all groups. All patients receive care in the stroke unit or neuro intensive care unit. Follow-up imaging studies will be obtained as computed tomography (CT) angiography at 24–48 h from the first infusion and subsequent magnetic resonance imaging within 24 h from the last infusion. Follow-up images play a role in the detection of adverse effects of the study drug.

All patients visit at the fourth week and third month after randomization. During follow-up, modified Rankin Scale (mRS) score, NIHSS score, and Barthel Index (BI) will be determined. Adverse events are collected throughout the study. Detailed follow-up schedules and procedures are shown in Fig. 3.

**Fig. 3 Fig3:**
[figure not shown]
Schedule of enrollment, interventions, and assessments in SONIC trial as per Standard Protocol Items: Recommendations for Interventional trials (SPIRIT)

### Blinding

Treatment assignment will remain blind in both the patient and treating physician except IP-preparing personnel. The IP-preparing personnel are not involved in any other aspect of the study. Study outcomes at baseline, day 7, the fourth week, and third month will be assessed with standardized forms and procedures by separate certified investigators blinded to the treatment. Finally, the Blinded-endpoint Monitoring Board will determine the primary endpoint through central adjudication. Results of neuroimaging will also be assessed by the imaging core laboratory team who are unaware of the treatment allocation.

### Study outcome

The primary outcome will be assessed by a dichotomous model: the proportion of patients with mRS 0–2 and that with mRS 3–6 at 3 months. Safety outcomes are all serious adverse events and symptomatic intracranial hemorrhage with neurologic deterioration (NIHSS score ≥ 4) on cerebral CT within 24–48 h after randomization [16]. The secondary outcomes are as follows: distributional change of mRS, difference in NIHSS score, ratio of NIHSS score 0–2, and ratio of BI ≥ 90 at 1, 4 weeks, and 3 months. All local principal investigators (PI) have a consensus meeting for imaging interpretation before the start of the trial and present regular meeting bi-annually.

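### Symptomatic intracranial haemorrhage has two incompatible windows (5 days and 24–48 h), and its NIHSS threshold is written as a score rather than a change

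*Protocol article*

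**What the plan says.** The outcome is described in two places in the protocol article.

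- Abstract, Methods paragraph: "Safety outcomes include symptomatic intracranial hemorrhage within 5 days".
- Methods, Study outcome: "symptomatic intracranial hemorrhage with neurologic deterioration (NIHSS score ≥ 4) on cerebral CT within 24–48 h after randomization", listed beside all serious adverse events.

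Three other sections bear on it.

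- Patient population, Table 1, requires "NIHSS ≥8 at screening time point".
- Treatment gives the dosing schedule: "Subsequent injection will be administered twice per day (12-h interval) during five consecutive days". It also gives the number of infusions: "The placebo group receives 250 mL of saline 10 times". The active arms have one larger initial dose and nine further doses.
- Treatment schedules the follow-up imaging as CT "angiography at 24–48 h from the first infusion and subsequent magnetic resonance imaging within 24 h from the last infusion", and states its purpose: "Follow-up images play a role in the detection of adverse effects of the study drug".

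**The concern.** There are three problems in one definition.

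1. **Window.** A symptomatic bleed on day 4 is an event under the Abstract and not an event under Study outcome.
2. **Time origin.** Study outcome counts from randomisation, while Treatment times the CT from the first infusion.
3. **Threshold.** The parenthesis gives an NIHSS score, not an increase, and names no reference value. Every eligible patient is already above 4 at screening.

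At stake is the symptomatic haemorrhage rate by arm, the only specific safety event that the Abstract and Study outcome name. With 70 patients per arm, each event moved in or out of the count changes an arm's rate by 1/70 = 1.4 percentage points. Two published definitions also leave room to choose between them after the data are seen.

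**Working it through.** **The plan's own figures.** The dose totals in Treatment reproduce: 750 + 9 × 500 = 5250 mg (high dose) and 500 + 9 × 250 = 2750 mg (low dose). The article gives no expected rate, power or sample size for haemorrhage, so there is no such figure to check.

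**Infusion times.** Take ten infusions exactly 12 h apart, with the first at or close to randomisation. They start at 0, 12, 24, 36, 48, 60, 72, 84, 96 and 108 h. Four start before 48 h, one is due at 48 h, and five start later.

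**Dose given after the 48 h limit.** The share is (number of later infusions × maintenance dose) / total dose.

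| Arm | 48 h infusion counted as inside | 48 h infusion counted as outside |
|---|---|---|
| High | 5 × 500 / 5250 = 48% | 6 × 500 / 5250 = 57% |
| Low | 5 × 250 / 2750 = 45% | 6 × 250 / 2750 = 55% |

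The range is therefore 45% to 57%. If the first infusion starts some time after randomisation, by up to 12 h, the fifth infusion starts more than 48 h after randomisation and the right-hand column applies.

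**Time after the 48 h limit.** Counting to the start of the last infusion, (108 − 48)/108 = 56%. Counting five full days, (120 − 48)/120 = 60%.

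**Coverage under the Abstract's window.** Five days is 120 h, and the last infusion starts at 108 h, so all ten infusions start inside it. The MRI is a separate matter. If the 24 h allowance is counted from the start of the last infusion, the scan may be as late as 108 + 24 = 132 h, which is after a strict 120 h limit.

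**The threshold.** Eligibility requires NIHSS of at least 8, and 8 ≥ 4. Read as an absolute score, the number is met by every eligible patient at screening. It can exclude only a patient who has since fallen below 4, and such a patient would not have deteriorated. As written, the number adds nothing to the words about deterioration.

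**The case against.** The strongest reply is that the trial does not lose these events. A reader might infer that later haemorrhages are missed altogether, but the article does not support that. All serious adverse events are a safety outcome with no 48 h limit, adverse events are collected throughout, an MRI follows the last infusion, the core laboratory reads haemorrhagic transformation (Imaging endpoints), and there is an adverse-event adjudication subcommittee (Study organization and data monitoring body). This stands as far as recording goes. It does not supply the defined rate: an adverse-event listing applies no symptomatic haemorrhage definition, and haemorrhagic transformation on a scan does not establish symptoms.

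A reader might also infer that improving patients or asymptomatic bleeds would be counted. The sentence requires the haemorrhage to be symptomatic and accompanied by deterioration, so such patients are not clearly included. A worsening of at least 4 points is the plausible intention. What remains is that neither the change nor its reference value is written down. The definition carries a citation that is not available here.

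Three further limits are fair:

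- The article does not call this the main safety endpoint.
- Saying that most of the dose falls after the window depends on how the 48 h infusion is counted, so only the range can be defended.
- A share of dose is not a share of haemorrhages, and the article gives no bleeding rate from which to estimate distortion between arms.

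Finally, an article condenses a fuller protocol (version 4.0), which may be clearer. That would excuse an omission. It does not excuse two stated rules that disagree.

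**Conclusion.** The point holds as an internal contradiction with a practical consequence. The two windows cannot both apply, the time origins differ, and the NIHSS threshold is not stated as a change. If the Study outcome text governs, 45% to 57% of the planned dose and 56% to 60% of the dosing period fall after the window closes. Symptomatic bleeds on days 3 to 5 would be left out of the rate by arm, and the MRI planned to detect adverse effects could not contribute to it. If the Abstract governs, the window takes in the start of every infusion.

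The percentages rest on exact 12 h spacing and on a first infusion close to randomisation. The contradiction itself rests on no assumption. Whether any arm comparison would change cannot be judged from the article. Severity: should-fix. The sample size and primary analysis are unaffected.

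**What to change.** Before unblinding, reconcile the Abstract, Study outcome and Treatment sections to a single definition of symptomatic intracranial haemorrhage that states:

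- one time origin, either randomisation or first infusion, used throughout;
- a window covering the 5-day dosing period, with its end worded so that the end-of-treatment MRI is clearly inside;
- evidence on CT or on the MRI already scheduled;
- an NIHSS increase of at least 4 points from a named reference value.

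Report the 24–48 h CT result as a supportive time point.

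No extra imaging and no change in sample size are needed. There are two costs. The reported count may rise because the window is longer. The NIHSS values used, both the reference and the one at deterioration, must also be ones the trial actually records. The Blinding section lists outcome assessments at baseline, day 7, week 4 and month 3, and the schedule figure is not shown, so a score at the time of deterioration cannot be assumed. Because recruitment is under way, the change should be dated and documented as made blind to allocation.
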